# Management of Chronic Non-Cancer Pain Through a Multicomponent Workshop Based on Non-Pharmacological Therapies: A Protocol for a Mixed-Methods Study, Including a Two-Arm Parallel-Group Randomized Clinical Trial and a Qualitative Component

**DOI:** 10.3390/healthcare14183063

**Published:** 2026-09-17

**Keywords:** chronic pain, non-pharmacological therapies, multicomponent workshop, randomized controlled trial, qualitative research, self-management

## Abstract

**Highlights:**

**What does this protocol contribute?**
This protocol describes a mixed-methods study comprising a two-arm parallel-group randomized controlled trial to evaluate a structured multicomponent workshop based on non-pharmacological therapies for chronic non-cancer pain, together with a qualitative component.This study is designed to assess the effectiveness, acceptability, and perceived usefulness of the intervention, while exploring how participants incorporate the strategies learned into daily life.

**What are the potential implications?**
This study may provide evidence to support the integration of structured non-pharmacological interventions into person-centered chronic pain care.The intervention may be transferable to other healthcare settings, including primary care and pain units.

**Abstract:**

**Background/Objectives**: Chronic non-cancer pain often requires approaches beyond pharmacological treatment. This protocol describes a mixed-methods study evaluating the effectiveness of a multicomponent intervention based on non-pharmacological therapies (NPhTs) and exploring participants’ post-intervention experience. **Methods**: The design includes a randomized, controlled, two-arm parallel-group clinical trial with 1:1 allocation, embedded within a mixed-methods approach that includes a qualitative phenomenological strand. This study will be conducted at Hospital San Juan de Dios del Aljarafe, Spain. A total of 160 adults with chronic non-cancer pain will be randomly assigned to the intervention or control group. The intervention group will receive five weekly 3.5 h face-to-face sessions combining pain education, emotional regulation, cognitive-motivational and mind–body techniques, lifestyle recommendations, peer support, and home practice, supported by a mobile application. The control group will continue usual care, without the workshop or intervention-related app content. The primary outcome will be change in the EuroQol-5D (EQ-5D) index from baseline to 1 month. Secondary outcomes will include the EQ-5D visual analogue scale (VAS) score, pain intensity, well-being, self-esteem, resilience, anxiety and depression, pain catastrophizing, medication use, and healthcare resource use. Outcomes will also be assessed at 4 months and, in the intervention group, at 7 months. Semi-structured interviews will explore the participants’ experiences, perceived usefulness of the techniques, and barriers and facilitators to maintaining the strategies learned. **Conclusions**: This protocol will evaluate the effectiveness and acceptability of a structured group-based NPhT intervention for chronic non-cancer pain. The findings may inform its applicability to person-centered and self-care-oriented models of care. **Trial registration:** ClinicalTrials.gov NCT06440668.

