### 2.2. Sample and Participants

#### 2.2.1. Sample Size

The sample size was determined based on the comparison between the two individually randomized study arms. The original calculation was based on a standardized difference of d = 0.50. A previous assessment of the same workshop population showed a standard deviation of approximately 0.197 for the EQ-5D index. Therefore, d = 0.50 corresponds to an absolute difference of approximately 0.10 EQ-5D index units. This correspondence is provided solely to contextualize the standardized effect used in the original sample-size calculation and is not a decision threshold for intervention effectiveness.

Using G*Power version 3.1.9.6 (Heinrich Heine University Düsseldorf, Düsseldorf, Germany) (two-tailed independent-samples *t*-test, α = 0.05, power = 0.80, 1:1 allocation, and standardized effect size d = 0.50), a total sample size of 128 participants, 64 per arm, was obtained. The complementary calculation for paired samples yielded a smaller sample size requirement and, therefore, did not determine the final sample size.

Because the primary endpoint is assessed at 1 month, the recruitment target was set to protect the primary analysis against the missing primary-outcome data at this time point. Based on previous workshop experience, approximately 20% of the randomized participants may fail to provide the 1-month assessment. Compensating for this anticipated loss requires 160 participants (128/0.80 = 160). To provide an additional operational margin for unanticipated missingness and later follow-up, this study will aim to recruit 180 participants (90 per arm). Later attrition may accumulate over the longer follow-up, but the 4-month and 7-month analyses are secondary or exploratory and do not determine the sample size for the primary endpoint.

Although the intervention is delivered in workshop groups, randomization is performed at the individual level and clustering occurs only in the intervention arm. A conventional cluster-randomized design effect, therefore, will not be applied. No empirical workshop-specific ICC was available to support a formal ICC-based inflation. Potential workshop-level correlation will be addressed prospectively using the prespecified partially nested mixed-effects model. The target of 180 participants provides additional recruitment margin beyond the formal individual-level requirement but is not presented as a formal ICC-adjusted power calculation.

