#### 2.2.3. Recruitment and Randomization

Potentially eligible patients will be identified by physicians from the hospital departments involved in the care of patients with CP, including Rehabilitation, Trauma and Orthopedic Surgery, and Internal Medicine. Patients may also be identified by primary care physicians in the hospital catchment area. These professionals, who provide care to patients with chronic non-cancer pain, are familiar with these workshops and have access to the applicable inclusion and exclusion criteria. When physicians at HSJDA identify a patient who, despite having received usual treatment for at least 6 months, continues to experience pain, the patient’s clinical report is sent to the hospital’s Patient Services Department with a request for inclusion in a workshop. The report is then forwarded by this department to the workshop coordinator. Primary care physicians send the patient’s information in encrypted form via the corporate email system of the Andalusian Public Health System to the workshop coordinator. Patients come from one of the 28 municipalities within the HSJDA catchment area (26 in the province of Seville and 2 in the province of Huelva). These patients are placed on a waiting list in order of referral date.

Each referred patient will be contacted by telephone to confirm eligibility. Eligible patients will receive information about the workshop and this study and will be invited to participate. Those who agree will receive the participant information sheet and informed consent form by email. These documents must be signed and returned before inclusion in this study.

The participants who provide informed consent will be added to the study candidate list in the MoviSalud platform. Subsequently, once a total of 40 patients is reached, the platform will subsequently perform computer-generated random allocation to either the intervention or the control group.

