#### 2.3.4. Data Management

The study data will be managed using the MoviSalud RPM (Remote Patient Monitoring) platform, adapted for this project. The platform will centralize data entered by the participants through the mobile app and will allow the research team to access these data through a professional web portal.

An internal medicine physician from the research team will conduct recruitment through a telephone interview to verify whether the patient meets the inclusion criteria. If eligible, the physician will inform the patient about this study and the possibility of being allocated to either the intervention or the control group and will obtain informed consent. Once a cohort of 40 patients has been recruited, the physician will notify the research support technician, who will register and enroll them in the app.

Once enrolled in the platform, the patient will have access exclusively to the baseline assessment forms prior to randomization. Once patients have completed the baseline assessment, randomization will be requested. Treatment allocation cannot be predicted in advance.

Allocation to the study arm will be performed automatically by the system through an atomic and irreversible transaction, with a timestamp and audit trail; no individual will be involved in the allocation process. The recruitment wave will then be closed, the corresponding workshop cohort will be established, and the control group will be activated. Within each combination of recruitment wave and stratum, permuted blocks of size 4 or 6 will be generated, with the block size selected randomly and independently for each block, with a probability of 0.50 for each size. With recruitment waves of approximately 40 participants divided into two sex strata, and considering the higher expected prevalence of women among individuals with chronic pain, the male stratum may comprise approximately 10–12 participants per wave. Blocks of size 8 would, therefore, result in a relatively high number of incomplete blocks at the end of each recruitment wave, which would be contrary to the intended purpose of blocking. Block sizes of 4 and 6 limit the maximum imbalance within each stratum to three participants, while preserving allocation unpredictability.

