### 2.5. Data Analysis

#### 2.5.1. Quantitative Analysis

Statistical analysis will be performed using IBM SPSS Statistics, version 27.0 (IBM Corp., Armonk, NY, USA). For categorical variables, absolute frequencies and percentages will be calculated. For quantitative variables, means and standard deviations (SDs) or medians and interquartile ranges will be reported, depending on whether the variables follow a normal distribution. This study has a single confirmatory primary analysis: the baseline-adjusted between-group difference in the EQ-5D index at 1 month, evaluated at a two-sided α level of 0.05. The EQ-5D contrast at 4 months and the prespecified secondary outcomes will be treated as supportive secondary analyses. Analyses of ad hoc outcomes, treatment-effect modification, subgroup analyses, per-protocol analyses, and the month-seven maintenance assessment will be considered exploratory. No global formal adjustment for multiplicity will be applied to these secondary and exploratory analyses because they will not be used to support independent confirmatory claims. Effect estimates and 95% confidence intervals will be emphasized; *p* values for secondary and exploratory analyses will be reported as nominal and interpreted cautiously in the context of multiple testing, and isolated nominal *p* values < 0.05 will not be considered confirmatory evidence.

Continuous secondary outcomes measured repeatedly will be analyzed using analogous linear mixed-effects models. Binary outcomes will be analyzed using logistic generalized linear mixed-effects models; count outcomes will be analyzed using Poisson or negative-binomial mixed-effects models, according to dispersion; and ordinal outcomes will be analyzed using an appropriate ordinal mixed-effects model when applicable.

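### The abstract says 160 participants will be randomized, but Section 2.2.1 sets a target of 180, and 180 is not a whole number of 40-patient waves

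*Protocol article*

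**What the plan says.** The abstract of the protocol article states the number randomized without qualification: "A total of 160 adults with chronic non-cancer pain will be randomly assigned to the intervention or control group".

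Section 2.2.1 (Sample Size) goes through three figures. The power calculation comes first: "a total sample size of 128 participants, 64 per arm, was obtained". This is divided by 0.80, because about one in five randomized participants may not provide the 1-month assessment, which gives 160. The section then adds a cushion for unforeseen missing data and later follow-up: "this study will aim to recruit 180 participants (90 per arm". It adds that 180 is not a power calculation adjusted for workshop clustering.

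Randomization runs in waves. Section 2.2.3 has the platform allocate "once a total of 40 patients is reached". Section 2.3.4 repeats 40 as the point at which a cohort is registered in the app. After baseline and allocation the wave is closed and its workshop cohort is set up. The same section is looser when it justifies the block sizes: "With recruitment waves of approximately 40 participants divided into two sex strata". The article does not give the number of waves or say how a last wave below 40 would be handled.

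**The concern.** The planned number randomized is one of the figures by which readers judge whether a trial ran as designed. Here the abstract and the sample-size section disagree on it by 20 participants. A reader of the abstract would take 160 as the plan and 180 as over-recruitment. A reader of Section 2.2.1 would take 180 as the plan and 160 as a shortfall. Either total could later be reported as the planned one.

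The wave rule adds to the ambiguity. The abstract's 160 is an exact number of 40-patient waves and the body's 180 is not. Because each wave creates one workshop, the total also decides how many workshops there are and how large the last one is. Those quantities bear on the partially nested analysis, for which the Limitations section already concedes that workshop groups are few.

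**Working it through.** **Inputs, all from the article.** Section 2.2.1 gives "α = 0.05, power = 0.80, 1:1 allocation, and standardized effect size d = 0.50" for a two-tailed independent-samples t-test, and "a standard deviation of approximately 0.197 for the EQ-5D index". Section 2.5.1 confirms that the primary contrast is "evaluated at a two-sided α level of 0.05". Anticipated loss at 1 month is 20% of those randomized. The wave trigger is 40.

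**Step 1: reproduce the plan's own figures.**
- Effect in index units: 0.50 × 0.197 = 0.0985, which the plan rounds to 0.10.
- Evaluable sample: the noncentral t gives 64 per arm as the smallest size with power of at least 0.80 (power 0.801). The normal approximation gives 63. The stated 128 reproduces.
- Allowance for loss: 128/0.80 = 160. This also reproduces.
- The 180 does not come from a formula. It is 160 plus a margin of 20, and 20/160 = 12.5%.

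**Step 2: are 160 and 180 the same kind of number?** Yes. The 20% loss is applied to randomized participants, so 160 is a number randomized, as the abstract also says. The 180 is split into 90 per arm, so it cannot be a number screened. The two statements therefore conflict.

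**Step 3: compare the totals.** With n analysed per arm, the noncentrality is d × √(n/2) on 2n − 2 degrees of freedom. The loss tolerated before the evaluable total falls below 128 is 1 − 128/N.

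| Randomized | Waves of 40 | Analysed per arm at 20% loss | Noncentrality | Power at d = 0.50 | Loss tolerated |
|---|---|---|---|---|---|
| 160 | 160/40 = 4 | 80 × 0.80 = 64 | 0.5 × √32 = 2.83 | 0.801 | 20.0% |
| 180 | 180/40 = 4.5 | 90 × 0.80 = 72 | 0.5 × √36 = 3.00 | 0.846 | 28.9% |

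These powers are at the individual level and ignore correlation within workshops.

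**Step 4: what the waves imply.** Four full waves give 160 and leave 180 − 160 = 20 participants. With 1:1 allocation and one workshop per wave, 160 means four workshops of about 20. A total of 180 means five workshops: either four of about 20 and one of about 10, or, with equal waves (5 × 36 = 180), five of about 18. Section 2.3.4 expects about 10–12 men in a wave of 40. In proportion, that is about 5–6 in a wave of 20 and about 9–11 in a wave of 36.

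**The case against.** The best defence is that the body of the article does fix a target. Section 2.2.1 labels each figure: 128 evaluable, 160 required after loss, 180 aimed for. Every calculation reproduces. On this view the abstract simply carries the required minimum where it should carry the target. That is correct, and it makes this a text inconsistency rather than a calculation error. It does not remove the conflict, because the abstract presents 160 as the number that will be randomized.

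A reader might go further and infer three things that the article does not support.

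- *That 180 cannot be reached.* The operational triggers say 40, but Section 2.3.4 also calls the wave size approximate, and nothing requires the last wave to be full. Blocks are generated within each wave and sex stratum, so the same scheme can allocate a smaller wave. The next full-wave total, 200, appears nowhere in the article.
- *That the two figures allow stopping or continuing according to results.* No interim analysis is described. The analyst is blinded and has no platform access (Section 2.1.1), data are cleaned and imported after collection ends (Section 2.3.4), and analysis falls in the final six months (Section 2.3.2). The trial is open-label, waves are sequential, and the research team can see participant-entered data through the portal (Section 2.3.4), so an explicit closing rule is a sensible precaution. The text shows no planned look at the data.
- *That the trial is underpowered.* Both totals meet the plan's 0.80 under its own assumptions.

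**Conclusion.** The point holds as a contradiction in the stated sample size: 160 randomized in the abstract against a target of 180 in Section 2.2.1, a gap of 20 participants or 12.5% of 160. The wave arithmetic supports a narrower statement. Since 180/40 = 4.5, reaching 180 needs a smaller last wave or unequal waves. The article permits this but does not say which will be used.

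The statistical consequence is modest. Individual-level power is about 0.80 at 160 and 0.85 at 180, assuming d = 0.50, 20% loss in each arm and no workshop correlation. This is a correction of the stated sample size and of the enrolment end point, not a power failure.

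**What to change.** 1. State one number to be randomized in both the abstract and Section 2.2.1. If the body's target stands, write 180 in the abstract and label 160 as the minimum required after 20% loss. Check that the registry entry agrees; that record was not available for this review.
2. Add a sentence that enrolment closes at that number regardless of accumulating data.
3. Make the waves consistent with the number. Either use equal waves that sum to it, for example five of 36, or keep 40 and say that a last wave of about 20 is allocated by the same blocked scheme. Either option is sufficient. Describe 90 per arm as approximate, since Section 2.3.4 accepts an imbalance of up to three participants within each stratum.

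The first two items, and the second option under the third, cost only text. Changing the wave size costs somewhat more: the block-size rationale in Section 2.3.4 is written for waves of about 40 and would need rechecking, the methodological lead would have to approve the changed parameter, and the ethics committee would have to be told if the change counts as substantial (Section 2.4). No extra workshop is needed, because 180 takes five under either option.

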## 1. Introduction

Chronic pain (CP) is defined as pain that persists or recurs for longer than 3 months or extends beyond the expected period of tissue healing [1]. It can be classified as chronic primary pain, in which pain constitutes a health condition itself, or chronic secondary pain, in which pain occurs in the context of an underlying condition [2].

CP affects an estimated 20–30% of adults worldwide [3,4,5], and 25.9% in Spain [6]. It has been associated with female sex, older age, lower educational level, unemployment, and greater healthcare resource use [7]. Consistent with the ICF framework, CP may involve impairments in body functions and, where relevant, structures, limitations in daily activities, and restrictions in social and occupational participation [8], alongside lower quality of life (QoL) [6]. The higher prevalence observed among women [6,7] supports considering sex and gender when examining the psychosocial impact of CP, coping strategies, and barriers to self-management.

Although pharmacological treatment remains an important component of CP management, it may be insufficient as a standalone approach and can involve adverse effects and adherence problems, particularly with long-term opioid use [9,10,11]. Current approaches, therefore, increasingly integrate pharmacological and non-pharmacological interventions within multimodal models of care [10,12,13,14].

Within these models, person-centered care considers patients’ experiences, needs, and preferences and promotes active participation in care, while self-management involves using skills and strategies to manage the physical, emotional, and everyday consequences of CP [13,14]. Non-pharmacological therapies (NPhTs) encompass physical, psychological, cognitive, mind–body, and lifestyle-related strategies that can support these goals by addressing different dimensions of CP [15]. NPhTs may be combined within multicomponent and multidisciplinary interventions [12,16].

### 1.1. Background

Multicomponent interventions combining several NPhTs have reported generally favorable pain-related, functional, and psychosocial outcomes in chronic non-cancer pain [16,17,18]. Evidence from multidisciplinary biopsychosocial rehabilitation for chronic low back pain suggests modest effects on pain and disability compared with usual care [19], while heterogeneity in intervention components, study designs, and follow-up periods limits conclusions regarding the effectiveness of specific programs [16]. The clinical relevance of these effects should, therefore, be interpreted cautiously.

The present study focuses on adults with chronic non-cancer pain, including both chronic primary and chronic secondary pain. Hospital San Juan de Dios del Aljarafe has delivered a multicomponent NPhT-based workshop for this population since 2016, using a standardized format since November 2021. The program consists of five weekly 3.5 h face-to-face sessions, integrating pain education, emotional regulation, cognitive and motivational strategies, mind–body techniques, lifestyle-related self-care, peer contributions, and home-based practice, with the aim of promoting active patient participation and the continued use of self-management strategies in daily life. Peer interaction is intended to promote shared learning, mutual support, and engagement with self-management strategies [20]. Previous qualitative and quasi-experimental evaluations of the workshop suggested improvements across pain-related, psychological, and QoL outcomes, as well as medication use and healthcare resource utilization [21,22,23]. However, these studies were conducted by the same research group within the same program and used non-randomized designs, limiting causal inference and leaving uncertainty regarding comparative effectiveness under randomized allocation and the longer-term maintenance of observed changes.

The present protocol addresses these uncertainties through a mixed-methods, randomized controlled trial. Random allocation will allow a more robust assessment of comparative effectiveness, while additional follow-up of the intervention group will explore longer-term outcome maintenance. Adherence will be monitored through session attendance, and a mobile application will support activity recording and continued self-management practice during follow-up, consistent with previous evidence on digital self-management support for chronic pain [24,25]. The qualitative strand will complement the trial by exploring the participants’ experiences, perceived usefulness of the intervention components, and personal or contextual factors that facilitate or hinder their incorporation into daily life—dimensions that cannot be fully captured through standardized outcome measures.

